#### ***Predisposing & reinforcing characteristics***

Information on predisposing characteristics of study participants is collected at baseline only, and include health access and insurance status, length of time in the US, acculturation, marital status, socioeconomic status, and personal and family history of T2DM. Measures were primarily drawn from the Behavioral Risk Factor Surveillance System (BRFSS) [35]. Information on reinforcing characteristics, including self-efficacy [36], social support and social capital [37], and religiosity are collected at each timepoint.

#### ***Knowledge and health behaviors***

At each time point, knowledge related to T2DM is assessed. Existing measures were adapted to assess diabetes management practices [38], knowledge acquired from each educational session, dietary practices [39], tobacco usage [35], patterns of physical activity [40], medication adherence [41], and mental health [42].

#### ***Knowledge and acceptability of CHWs***

At each follow-up timepoint, we assess the mechanisms through which CHWs operate to fulfill their role as a bridge to the healthcare system and advocates for their community. A measure to assess these mechanisms included items related to trust, communal concordance, honesty, communication, empowerment, and resource linkages. Table 1 outlines all of the above measurement domains & data collection timepoints in more detail.

**Table 1 T1:** Measurement domains & data collection timepoints

**Component**	**Baseline**	**3 MOS**	**6 MOS**	**12 MOS**
**Socio-demographic (pre-disposing characteristics):**				
Sex, age, marital status, country of birth, years in U.S., education, household size, home language, English fluency	✓			
Employment Status	✓	✓	✓	✓
Health insurance	✓			
Barriers to healthcare	✓			
**Reinforcing characteristics:**				
Social support	✓	✓	✓	✓
Self-efficacy	✓	✓	✓	✓
Social capital	✓	✓	✓	✓
Religiosity	✓	✓	✓	✓
**Knowledge and health behaviors:**				
Diabetes knowledge	✓	✓	✓	✓
Diabetes management	✓	✓	✓	✓
Dietary practices	✓	✓	✓	✓
Food behavior	✓	✓	✓	✓
Tobacco use	✓	✓	✓	✓
Physical activity	✓	✓	✓	✓
Medication adherence	✓	✓	✓	✓
Mental health	✓	✓	✓	✓
**Clinical measurements:**				
HbA1c	✓	✓	✓	✓
Blood pressure	✓	✓	✓	✓
Height				✓
Weight	✓	✓	✓	✓
BMI	✓	✓	✓	✓
Waist, Hip, Waist-to-Hip ratio	✓	✓	✓	✓
Lipid profile	✓	✓	✓	✓
**Knowledge and acceptability of CHWs**				
	✓	✓	✓	
**Program evaluation**				
				✓

### Data analyses

Analyses to compare the treatment and control group participants are conducted at baseline to detect significant differences. Student t-tests for normally distributed variables (after necessary transformations) and chi-squared tests for categorical variables were used. In the event that randomization did not control for differences between the treatment and control groups on baseline characteristics, we statistically controlled for those differences in subsequent analyses of program effects. Descriptive statistics are conducted to characterize study participants and to evaluate the distribution of key exposure and outcome variables, as well as to describe the factors that affect utilization of health care services and the risk and protective factors for diabetes. Summary data on medical history, length of time in the US, access and utilization to primary health care services, and social characteristics (e.g., marital status, employment, education) is reported.

The primary goal of this study is to evaluate intervention efficacy, using the generally accepted approach in evaluating efficacy trials, Intention to Treat (ITT) [43]. The analysis for each aim will be comprised of t-tests for continuous variables and chi-square tests for categorical variables. Indexes will be created for scale variables and examined as continuous variables. Mann–Whitney U Tests will be applied for indices with non-parametric distributions.

Each aim will be tested using multivariate logistic regression analysis. The base model will consider the intervention group as the primary predictor variable. Interaction terms between treatment and follow-up time will be developed to assess whether the effect of treatment varied over time. A third set of models included other covariates identified in the preliminary analysis as potential confounders that may reduce the likelihood of confounding bias. Goodness-of-fit of the final models will be assessed using the Hosmer-Lemeshow test.

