### Study design

Aggregated patient registry data from a large, public hospital in NYC was used to gauge the approximate size of the community served at this particular healthcare institution. A targeted enrollment of n = 256 was used for this study as previously described in the power calculation. The projected sample size also takes into account previous literature detailing refusal and attrition rates for peer- and CHW-led health interventions [21-23].

The study is a two-arm RCT design. Following screening, consenting, and study enrollment, participants are randomly assigned to either treatment or control group by a blinded study staff member using IBM SPSS Statistics, Version 19.0 (IBM Corp). Study groups are stratified by gender and age. Both study staff and participants are notified of subject randomization allocation. Additionally, all participants randomized to the control groups are offered the opportunity to receive the full intervention after serving as a control for the 6-month study period. This strategy is part of a multi-pronged effort to improve data collection rates among participants randomized to the control group, as well as an effort to conduct the study in alignment with the principles of community-based participatory research (CBPR) and in response to community concerns regarding the ethics of withholding potentially beneficial interventions for community members.

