### Data collection

Data collection occurs with treatment and control group participants at Baseline, 3-Month, and 6-Month timepoints, with a +/- 30 day window. Additionally, the treatment group is contacted at the 12-Month timepoint to obtain long-term follow-up information. Within the clinical setting, providers collect Hemoglobin A1c (HbA1c) levels and lipid profile according to the standard of care lab schedule for management of each participant. Outside of the clinical setting, questionnaire data and several clinical endpoints (height, weight, blood pressure, and waist/hip circumference) are obtained; all procedures are completed in-language by CHWs or trained study personnel. In addition to the above timepoints, questionnaire data is collected at each one-on-one visit pertaining to access and utilization of primary and specialty care, as well as barriers encountered in maintaining a healthy diet, engaging in physical activity, and managing stressors. Figure 3 demonstrates procedures for each study group and overall flow of study design.

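### Adjustment is triggered by observed baseline differences, so the plan does not secure baseline HbA1c or the stratification factors in the treatment comparison

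*Protocol article*

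**What the plan says.** All of the analysis text is in the protocol article under Data analyses. It begins with baseline testing: "Analyses to compare the treatment and control group participants are conducted at baseline to detect significant differences". Adjustment follows from what is observed: "In the event that randomization did not control for differences between the treatment and control groups on baseline characteristics", those differences are controlled for in the later analyses of program effects.

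Two routes are then given for the treatment comparison. The first is "The analysis for each aim will be comprised of t-tests for continuous variables and chi-square tests for categorical variables". The second is "Each aim will be tested using multivariate logistic regression analysis", and for it "The base model will consider the intervention group as the primary predictor variable". Treatment-by-time interaction terms come next. After them, "A third set of models included other covariates identified in the preliminary analysis as potential confounders".

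Two other sections matter. Under Study design, "Study groups are stratified by gender and age". Under Data collection, "Data collection occurs with treatment and control group participants at Baseline, 3-Month, and 6-Month timepoints", and Table 1 lists HbA1c at baseline. No section commits to including baseline HbA1c, gender or age in the treatment comparison.

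**The concern.** In a randomised trial, a significant baseline difference is a chance event. It says nothing about whether the variable predicts the outcome, and only prognostic strength determines what adjustment gains. A rule keyed to observed imbalance therefore tends to pick the wrong variables. It would usually leave out baseline HbA1c, the most plausible predictor of 6-month HbA1c, and it might bring in weak covariates that happened to differ.

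Two things are at stake. The first is precision, in a trial whose own sample size section asks for 120 per group to detect 0.3 but expects 96 per group at 6 months. The second is that the adjustment set is fixed only after data are seen, in a trial where staff know the allocation.

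**Working it through.** **Inputs from the article (Sample size calculations).** Differences of 0.5 and 0.3 in HbA1c, power 0.8, significance level 0.05, n = 40 and 120 per group; 75% retention giving 96 per group.

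**Assumed, because not stated.** Two-sided testing; the SD; the correlation r between baseline and 6-month HbA1c; a 0.05 threshold for calling a baseline difference.

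**1. Recovering the plan's own figures.** For two means, n per group = 2(1.960 + 0.842)² SD²/d² = 15.70 SD²/d², so SD = d√(n/15.70).
- From 40 per group: 0.5 × √(40/15.70) = 0.798.
- From 120 per group: 0.3 × √(120/15.70) = 0.829.
- A common SD of 0.817 gives 42 and 117, close to both stated figures.

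This is the unadjusted formula, with no allowance for baseline correlation. Retention reproduces: 128 × 0.75 = 96.

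**2. Unadjusted power at 96 per arm, difference 0.3.** SE = 0.817 × √(2/96) = 0.1179. Then 0.3/0.1179 = 2.544, and Φ(2.544 − 1.960) = 72%.

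**3. Analysis of covariance on baseline HbA1c.** The SE is multiplied by √(1 − r²).

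| r | √(1 − r²) | 0.3/SE | Power | n per arm for 80% power |
|---|---|---|---|---|
| 0 | 1.000 | 2.544 | 72% | 117 |
| 0.3 | 0.954 | 2.667 | 76% | 106 |
| 0.4 | 0.917 | 2.776 | 79% | – |
| 0.5 | 0.866 | 2.938 | 84% | 88 |
| 0.6 | 0.800 | 3.180 | 89% | 75 |

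At r = 0.5, 96 completers carry the information of 96/0.75 = 128 under the plain t-test. The difference detectable with 80% power is 2.802 × 0.1179 = 0.33 unadjusted, and 0.33 × 0.8 = 0.26 at r = 0.6.

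**4. If the t-test is on change from baseline.** The SE is multiplied by √(2(1 − r)). At r = 0.5 this factor is 1, so power stays at 72%. At r = 0.6 it is 0.894, giving 81% (82% with SD 0.81). Change scores never beat covariance adjustment, because 2(1 − r) − (1 − r²) = (1 − r)² ≥ 0.

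**5. The conditional rule, simulated** (40,000 runs per setting, 96 per arm, SD 0.83; adjust for baseline HbA1c only if its baseline p<0.05). Baseline HbA1c is flagged in about 5% of runs.

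| r | Power: t-test | Power: conditional rule | Power: always adjusted | Type I error: conditional rule |
|---|---|---|---|---|
| 0.5 | 69.8% | 70.8% | 81.8% | 4.3% |
| 0.7 | 70.2% | 72.2% | 93.4% | 3.5% |

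The rule recovers very little of the available gain, and its type I error is below nominal.

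**6. Chance flags.** With k independent baseline tests at 0.05, the probability of at least one flag is 1 − 0.95^k: 40% for k = 10 and 64% for k = 20. Those values of k are illustrative.

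**The case against.** Several objections deserve weight.

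**The t-test is not declared the main comparison.** A reader might infer that it is. The article also says each aim is tested by logistic regression, which does not suit HbA1c as a continuous measure, and it ranks neither route. What stands is that both start unadjusted: no covariates are named for the t-test, and the base model names only the intervention group.

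**Covariates may enter by another route.** A reader might infer that only a baseline significance test lets a covariate in, and hence that baseline HbA1c is ignored in about 95% of trials. The text does not support that. It gives no threshold, and the preliminary analysis that feeds the third set of models is not defined as baseline testing alone. Baseline HbA1c could appear there. It is still selected from the data and not committed to in advance.

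**Change scores would use baseline HbA1c.** The abstract's outcome list mentions change, and the sizing drew on changes seen in a pilot. But the sizing compares group levels (6.7 vs 6.2), and the analysis section does not say that change is tested. If it is, the gain from covariance adjustment shrinks at higher correlations but does not vanish.

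**The correlation may be modest.** Entry requires HbA1c of at least 6.5%, which truncates the baseline range and may lower r. At r = 0.3 the gain is about 4 points.

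**Detail may sit in an unseen analysis plan.** That could cover the choice of one primary model. It does not cover the baseline-testing rule, which is stated text.

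**Validity is not broken.** A reader might infer an inflated false-positive rate. The conditional rule alone is conservative. In the same simulation, type I error reached 7.3% (r = 0.5) to 8.4% (r = 0.7) only if either the unadjusted or the adjusted result could be claimed, and the article does not say that it may be.

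**Conclusion.** The point holds as an efficiency and prespecification weakness. The stated rule ties adjustment to chance differences, starts from unadjusted comparisons, and leaves baseline HbA1c, gender and age uncommitted.

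At 96 per arm and a difference of 0.3, prespecified adjustment for baseline HbA1c raises power from about 72% to between 76% and 89% for r from 0.3 to 0.6. It reaches 80% somewhere between r = 0.4 and r = 0.5. These figures rest on an SD of about 0.82 back-solved from the article's sample sizes, two-sided testing, and an assumed r; the article gives none of these. The 5% flagging rate rests on an assumed 0.05 threshold. The gain from adding gender and age was not quantified; they belong in the model because allocation was stratified by them.

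**What to change.** - For 6-month HbA1c, prespecify a linear model with arm, baseline HbA1c, gender and age. Analyse other continuous outcomes in the same way, each with its own baseline value.
- Remove baseline significance testing as the trigger for adjustment, and present baseline tables descriptively.
- Label models with further covariates as sensitivity analyses.

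The cost is a change of analysis wording. It should be dated before outcomes are examined, because recruitment began in February 2011 and staff are not blinded. One practical matter needs a rule: HbA1c comes from the standard-of-care laboratory schedule, so the plan must say which value counts as baseline and how a missing one is handled. Eligibility itself requires an HbA1c result, so a wholly absent value should be uncommon, but its timing may vary.

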### Sample size calculations

The size of the study population is based on the primary outcome measure of HbA1c and was estimated by using previous changes observed in a pilot study as well as in previous research [19,20]. Control group HbA1c estimates were based on hospital patients receiving usual care. An absolute difference of 0.5% in HbA1c between the groups (6.7 vs. 6.2) with a power of 0.8 and significance level of 0.05 may be detected with a total of 40 individuals in each group, and an absolute difference of 0.3% in HbA1c between the groups (6.7 vs. 6.4) with a power of 0.8 and significance level of 0.05 may be detected with a total of 120 individuals in each group. The sample size calculation was based on a medium effect size of the primary outcomes between the intervention and control group. Approximately 256 enrolled study participants were randomized each to the treatment and control groups. We anticipated that 75% of study participants would be followed to completion of the study at 6 months (n = 96 in each group).

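### Two unreconciled analyses are named for every aim, and the only one with adjustment and treatment-by-time terms, logistic regression, does not suit continuous HbA1c

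*Protocol article*

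**What the plan says.** The Sample size calculations section of the protocol article states: "The size of the study population is based on the primary outcome measure of HbA1c". The calculation compares means: "An absolute difference of 0.5% in HbA1c between the groups (6.7 vs. 6.2) with a power of 0.8 and significance level of 0.05". For that difference it gives 40 per group; for a 0.3 point difference (6.7 vs 6.4) it gives 120 per group. Under Study outcomes, HbA1c is listed as a level to be lowered; the clinical outcomes include a proportion only for controlled blood pressure. The one HbA1c threshold in the article, 6.5%, is an entry criterion.

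The Data analyses section then names two analyses, each for every aim:

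- **Simple tests:** "The analysis for each aim will be comprised of t-tests for continuous variables and chi-square tests for categorical variables", with Mann–Whitney tests for indices that are not suitably distributed.
- **Regression:** "Each aim will be tested using multivariate logistic regression analysis". Study group is the main predictor. A further step adds time: "Interaction terms between treatment and follow-up time will be developed to assess whether the effect of treatment varied over time". A third set of models adds possible confounders. The check on fit is: "Goodness-of-fit of the final models will be assessed using the Hosmer-Lemeshow test".

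The same section says that baseline imbalances will be controlled for in the later analyses of programme effects. HbA1c is scheduled at baseline, 3 and 6 months in both arms. For later data, the Data collection section says: "Additionally, the treatment group is contacted at the 12-Month timepoint to obtain long-term follow-up information".

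**The concern.** Logistic regression needs a categorical outcome, and the Hosmer-Lemeshow test indicates that a binary one is meant. HbA1c, the outcome on which the trial is sized, is continuous. The t-test suits it, but a t-test cannot adjust for baseline differences, include confounders or examine treatment by time. The article promises all three, and the only model it offers for them is logistic.

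An adjusted or longitudinal HbA1c result would therefore need a cut-point that the article does not state. Three things are at stake:

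- **Estimate:** an odds ratio for crossing a threshold is not the 0.3 to 0.5 point difference the trial was designed to detect.
- **Power:** dichotomising a continuous measure discards information.
- **Freedom of choice:** with no cut-point and no primary analysis named, either could be picked after the results are seen, in a trial where staff and participants know the allocation.

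**Working it through.** **1. Does the sizing fit a comparison of means?** The article gives differences, power 0.8 and significance level 0.05, but no SD and no sidedness. Two-sided testing is assumed.

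Formula: n per group = 2 × (1.96 + 0.8416)² × SD² / d² = 15.70 × SD² / d².

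- 40 per group, d = 0.5: SD = √(40 × 0.25 / 15.70) = 0.798.
- 120 per group, d = 0.3: SD = √(120 × 0.09 / 15.70) = 0.829.
- One SD of 0.817 gives 42 and 117 per group, close to the stated 40 and 120.

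The figures cannot be reproduced exactly without an SD, but they fit a two-sample comparison of means with SD of about 0.80 to 0.83. The expected completers reproduce: 256 / 2 × 0.75 = 96 per arm.

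**2. Power on the mean, d = 0.3, 96 per arm, SD 0.817.**

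Standard error = 0.817 × √(2/96) = 0.1179. Power = Φ(0.3/0.1179 − 1.96) = Φ(0.584) = 0.72.

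**3. Power if HbA1c is dichotomised.** The cuts of 6.5 and 7.0 and a normal distribution are assumptions. The proportion at or above cut c is 1 − Φ((c − mean)/SD). Power is for a two-sided comparison of two proportions, with pooled variance under the null.

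| Cut | Mean 6.7 | Mean 6.4 | Power, 96 per arm | n per arm for 0.8 |
|---|---|---|---|---|
| 6.5 | 0.597 | 0.451 | 0.52 | 185 |
| 7.0 | 0.357 | 0.231 | 0.48 | 207 |

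Worked for 6.5: difference 0.1454, null standard error 0.0721, alternative standard error 0.0713. Power = Φ((0.1454 − 1.96 × 0.0721)/0.0713) = Φ(0.06) = 0.52.

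Over SD 0.80 to 0.83, power on the mean is 0.74 to 0.71. Dichotomised, it is 0.54 to 0.51 at 6.5 and 0.49 to 0.47 at 7.0. Either cut needs more than the 128 per arm to be enrolled to reach 0.8.

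**4. A conditional check: repeated visits.** The article does not say that visits are treated as independent. If they were, with two follow-ups per person, the variance factor is 1 + ρ for a treatment term pooled over visits and 1 − ρ for treatment by time. Here ρ is the correlation of the binary records. For a cut near the median, ρ = (2/π) × arcsin(r), where r is the correlation of the underlying HbA1c values (assumed 0.5 to 0.8). The true error rate is 2 × (1 − Φ(1.96/√factor)). The simulation used ordinary logistic regression, cut 6.5, no treatment effect, 96 per arm and 1,500 runs per setting.

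| r | ρ | Pooled treatment: formula / simulated | Treatment by time: formula / simulated |
|---|---|---|---|
| 0.5 | 0.33 | 0.090 / 0.085 | 0.016 / 0.017 |
| 0.7 | 0.49 | 0.109 / 0.111 | 0.006 / 0.009 |
| 0.8 | 0.59 | 0.120 / 0.116 | 0.002 / 0.003 |

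With person-clustered standard errors, the pooled treatment term returned to 0.043 to 0.049 in the same simulations.

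**The case against.** The strongest reply is that a valid HbA1c test is already in the plan. The t-test is named for continuous variables in every aim, matches the sizing, estimates the mean difference and keeps the 0.72 power. That stands: HbA1c is not left without a suitable test, and the article never labels the logistic model confirmatory. It does not remove the conflict, because both analyses are assigned to every aim, neither is called primary, and the t-test cannot deliver the promised adjustment or time terms.

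Three stronger readings are tempting, and the document does not support them:

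- **The plan ignores within-person correlation, so its error rate is wrong.** This would be inferred from silence. A condensed article may leave GEE, random effects or robust variances to a fuller document, and the base model could be fitted at 6 months alone. The direction also differs by term: the pooled treatment term would reject too often and the treatment-by-time test too rarely. With categorical visits and the interaction in the model, the treatment coefficient at the reference visit uses one record per person and keeps its nominal level.
- **The inflation reaches that of three pooled visits.** Both arms have only two visits after baseline. A third record would be baseline, where no effect exists, or 12 months, where there are no controls.
- **One-arm 12-month data contaminate the between-arm model.** Nothing places them there. The article describes a 6-month trial and calls the 12-month data long-term follow-up.

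The power losses also depend on chosen cuts. That is fair, but it is a consequence of the article giving none.

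**Conclusion.** The point holds as a conflict between two stated analyses and a mismatch between the named regression and the outcome that sized the trial. The model type is stated, so the brevity of an article does not explain it.

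If the logistic model is used for HbA1c, power for a 0.3 difference at 96 per arm falls from about 0.72 to about 0.5: 0.52 or 0.48 at SD 0.817, and 0.47 to 0.54 over SD 0.80 to 0.83. This rests on the implied SD, normality and cuts at 6.5 or 7.0, none of which the article gives. The 0.3 to 0.5 point difference would not be estimated at all. The unadjusted t-test is untouched.

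The error rates of about 0.09 to 0.12 for the pooled treatment term, and 0.02 or less for treatment by time, apply only if visits are pooled as independent. They are a reason to state the method, not a finding that the plan's error rate is wrong.

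**What to change.** Before the final analysis, replace the sentence that assigns logistic regression to every aim with text to this effect:

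- **Primary analysis:** the difference in mean HbA1c at 6 months between the randomised arms, from a linear model adjusted for baseline HbA1c and the stratification factors gender and age. A linear mixed model over 3 and 6 months with treatment, visit and treatment by visit is an equally acceptable choice; name one.
- **Other continuous outcomes:** the same type of model. State that the t-tests are supportive.
- **Binary outcomes, such as controlled blood pressure:** logistic regression, with GEE or a random intercept when visits are combined. Do not rely on Hosmer-Lemeshow for those repeated-measures models.
- **Safeguard:** between-arm models stop at 6 months, because 12-month data exist only in the treatment arm and controls are offered the full intervention after 6 months. Report the 12-month data as within-arm description.

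The cost is a wording change in the Data analyses section. All variables are already scheduled for collection, and no further participants are needed.
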